**Study design:**

This prospective study will be performed in patients with severe aortic valve stenosis. To assess the occurrence of cerebral infarction, all patients will undergo cerebral DW-MRI and neurological assessment within 24 hours before, and 48 hours after cardiac catheterization and retrograde catheterization of the aortic valve. Randomization for the access site will be performed before coronary angiography. A subgroup will be monitored by transcranial power M-mode Doppler during cardiac catheterization to observe cerebral blood flow and track emboli. Neuropsychological tests will also be recorded in a subgroup of patients before and after the interventional procedures to assess the impact of silent brain injury on potential cognitive decline. The primary end-point of the study is a direct comparison of ischemic cerebral lesions as detected by serial cerebral DW-MRI between patients explored by radial access and patients explored by femoral access. Secondary end-points include comparison of neuropsychological test performance and number of microembolism signals observed in the two groups.

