In the present trial two vascular access sites (trans-radial approach [TRA] and trans-femoral approach [TFA]) routinely used for cardiac catheterization and percutaneous cardiovascular interevention (PCI) will be compared for the risk of silent brain injury occurrence. Indeed TRA is associated with fewer local complications and it has been suggested that in particular right TRA, which avoids crossing the aortic arch could reduce the risk of mobilization of atherosclerotic plaque, present particularly within the aortic arch as documented previously by several authors [12-14]. However this risk of brain injury in relation to vascular access site remains largely debatable. Using DW-MRI as a surrogate parameter for brain injury assessment we propose a prospective evaluation of the occurrence of silent brain lesions in patients randomized either to TRA or TFA.

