### Neuropsychological assessment

Patients will undergo neuropsychological assessment within 24 hours before, and 48 hours after, cardiac catheterization. All patients with documented cerebral infarction at DW-MRI will be asked to come back for a new neuropsychological assessment at 1 year follow-up.

The aim of the cognitive testing is to provide clinical evidence of potential cerebral damage after cardiac catheterization and to quantify this potential cognitive decline allowing comparison of two groups of patients explored either by radial or femoral approaches. The tests must be sensitive enough to detect potential post-procedure cognitive decline and also able to explore different brain areas. Most of the neuropsychological tests that will be administered have been reported to be sensitive to change after CABG or PCI procedures [19] and will include: Digit Span Forwards and Backwards, Trail making test A and B, Wechsler Memory Scale visual reproduction test, Rey-Osterrieth's figure test, Grober-Buschckle's test, Rey Auditory Verbal Learning Test, Verbal fluency test, and Confrontation naming test.

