### Statistical analysis

Baseline characteristics of the study population will be presented as counts and percents for categorical variables and as mean ± SD for continuous variables. Kappa statistic will be calculated to determine interobserver agreement. The number of lesions in our population of patients recruited will be estimated by the adjusted Wald interval at 95% in accordance with the method recommended by Agresti & Coull [20]. With small sample sizes, as recommended we will use the mid-point of the adjusted Wald interval instead of the observed proportion [21]. The statistical analyses will be performed using SPSS 10.0.7 software (Chicago, IL, USA). The compound score for global cognitive function will be constructed by calculating the average of the z scores for all the above tests. Cognitive decline will be calculated by subtracting the z scores for memory performance, psychomotor speed, and global cognitive function at follow-up from the z scores at base line. All analyses will be adjusted for age, sex, and level of education, as well as the interval between the two sets of neuropsychological tests.

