### Randomization

After informed consent, eligible patients are randomized 1:1 to a strategy of radial or femoral access. Randomization will be performed at the catheterization laboratory before coronary angiography, by means of randomization list (sealed envelopes) prepared by blocks of 10 patients.

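### The randomised radial-versus-femoral cognitive comparison is adjusted for the interval between test sessions, which is completed only after allocation; under conditions the protocol neither states nor rules out, this may bias the contrast

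*Protocol article*

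**What the plan says.** The adjustment rule closes the Statistical analysis section, straight after the definition of the cognitive scores: "All analyses will be adjusted for age, sex, and level of education, as well as the interval between the two sets of neuropsychological tests". Nothing limits it to one type of comparison.

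The comparison by access route is one of the cognitive analyses. The Study design paragraph of the Abstract states: "Secondary end-points include comparison of neuropsychological test performance and number of microembolism signals observed in the two groups". The Neuropsychological assessment section gives as an aim of testing to "quantify this potential cognitive decline allowing comparison of two groups of patients explored either by radial or femoral approaches".

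The order of events comes from two sections. On testing: "Patients will undergo neuropsychological assessment within 24 hours before, and 48 hours after, cardiac catheterization". On allocation: "Randomization will be performed at the catheterization laboratory before coronary angiography".

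**The concern.** Randomisation protects a comparison only as long as the analysis conditions on nothing that allocation can change. Three of the four covariates meet that test and the interval does not. Its first part, from baseline test to procedure, is settled before the envelope is opened. Its second part, from procedure to retest, comes after.

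The protocol itself offers a possible link between arm and timing. The Background says that "TRA is associated with fewer local complications". A patient with a complication might be retested later and might also score worse. Adjusting for the interval could then remove part of the access-site effect, or create an association between arm and score that does not come from the route. What is at stake is the interpretation of one secondary comparison.

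**Working it through.** **The plan's own figure.** The only sample-size figure is 152 (76 per arm) for the DW-MRI end-point, from rates of 5.9% and 23%, alpha 5% and power 80% (Sample size calculation). The two-sided formula for two proportions gives 66 per arm. With continuity correction it gives 77 per arm, 154 in total, within two patients of the stated figure. The test interval plays no part in it. The cognitive comparison has no stated figure to reproduce.

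**How much of the interval follows allocation.** Taking the windows as up to 24 h before and up to 48 h after, the in-window maximum is 24 + 48 = 72 h (plus the procedure). Up to 48/72, or two thirds, arises after allocation.

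**Precision.** Let d be the arm difference in mean interval, in within-arm SDs. With 1:1 allocation the squared correlation of arm and interval is r² = d²/(d² + 4), so the variance inflation is 1/(1 − r²) = 1 + d²/4, when the interval does not predict the score:

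- d = 0.1: 1.00 (SE +0.1%)
- d = 0.25: 1.02 (SE +0.8%)
- d = 0.5: 1.06 (SE +3.1%)
- d = 1: 1.25 (SE +11.8%)

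**Bias.** In a linear model, adjusted effect = total effect − (within-arm slope of score on interval) × (arm difference in interval). Both factors must be non-zero for the estimate to move.

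The following inputs are assumptions, not in the protocol: 76 tested per arm, residual SD of decline 1, a lesion adds 0.5 SD of decline, residual SD of the interval 10 h. With the protocol's lesion rates the lesion-mediated effect is 0.5 × (0.23 − 0.059) = 0.0855 SD more decline with femoral access. Simulated means over 5,000 runs:

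| Assumed situation | Unadjusted | Adjusted | Variance ratio |
|---|---|---|---|
| Arm does not move timing; timing unrelated to score | 0.082 | 0.082 | 1.00 |
| Arm does not move timing; decline rises 0.03 SD per hour | 0.085 | 0.085 | 0.94 |
| Femoral retested 6 h later, nothing else | 0.086 | 0.086 | 1.09 |
| Femoral 6 h later; a lesion delays retest by 12 h | 0.084 | 0.037 | 1.12 |
| Femoral 6 h later; frailty delays retest (6 h per SD) and worsens score (0.5 SD per SD) | 0.086 | −0.045 | 1.02 |
| Femoral 6 h later; timing itself adds 0.01 SD of decline per hour | 0.146 | 0.086 | 1.09 |

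Hand check of the fourth row. Mean within-arm lesion variance is (0.059 × 0.941 + 0.23 × 0.77)/2 = 0.116. The slope is 0.5 × 12 × 0.116 / (100 + 144 × 0.116) = 0.0060 per hour. The arm difference in interval is 6 + 12 × 0.171 = 8.05 h. Adjusted effect: 0.0855 − 0.0060 × 8.05 = 0.037.

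Hand check of the fifth row. The slope is 0.5 × 6 / (36 + 100) = 0.022 per hour. Adjusted effect: 0.0855 − 0.022 × 6 = −0.047, against −0.045 simulated.

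**Against the standard error.** The fourth row moves the estimate by 0.047 with an unadjusted SE of 0.165, about 0.3 SE. The fifth moves it by 0.131 with an SE of 0.183, about 0.7 SE. If only 60 patients were tested (an assumption), the SE would grow by √(152/60) = 1.59 and these become about 0.2 and 0.5 SE.

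**The case against.** The strongest reply is that the harm needs two links the protocol does not contain: that the arm shifts retest timing, and that timing is tied to the score by a mediator or common cause. The Background speaks of local complications, not of delayed testing or worse cognition, and both arms share one retest window. If the retest is meant at a fixed 48 h rather than within 48 h, the part of the interval after allocation would hardly vary. This stands, and it is why the point is conditional.

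A second reply also has force. If timing affects scores directly and differs by arm, the unadjusted contrast carries a timing component (0.146 against 0.086 in the last row), and some would want it removed. That supports a sensitivity analysis. It does not support making the adjusted estimate the only one, because the data cannot easily tell this situation from the two before it.

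Third, the list of secondary end-points and the third study objective frame cognition as a consequence of infarction, a non-randomised question where interval adjustment is reasonable. But the Abstract and the Neuropsychological assessment section also name the comparison by arm, and the adjustment sentence makes no distinction.

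A reader might go further and connect the rule with the one-year visit: "All patients with documented cerebral infarction at DW-MRI will be asked to come back for a new neuropsychological assessment at 1 year follow-up". Decline is defined from scores at follow-up ("Cognitive decline will be calculated by subtracting the z scores for memory performance, psychomotor speed, and global cognitive function at follow-up"). If one-year scores entered the same model, the interval would nearly identify the infarct patients. The protocol does not say that one-year and 48-hour scores will be pooled, so this reading is not supported.

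**Conclusion.** The point holds in conditional form. The rule as written conditions a randomised secondary comparison on a variable completed after allocation, so its estimate may not be the effect of the assigned route. The documents do not support the stronger inference that the estimate is biased as the plan stands, or that adjustment must cost precision: with no arm difference in timing there is no bias, and precision may improve slightly (variance × 0.94 in one assumed case).

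The size is unknown. Every bias figure above rests on assumed delays and effects. The Abstract places neuropsychological testing in a subgroup, so 152 tested is an upper bound. With a shared and short window the effect is probably small. Nor should the rule be read as reaching the DW-MRI comparison: it follows the cognitive score definitions, and the primary end-point and the sample size of 152 are untouched. This is a cheap improvement, not a serious defect.

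**What to change.** In the Statistical analysis section, separate the two kinds of cognitive analysis:

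- For the radial-versus-femoral contrast, adjust only for variables measured before allocation: age, sex and level of education.
- Report the interval between test sessions by arm, so that a reader can see whether timing differed.
- Keep adjustment for the interval for a sensitivity analysis of that contrast, or for the non-randomised analysis of infarction and cognition.

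The change is about one sentence and needs no new data. Its cost is a possible small loss of precision if the interval predicts the score and is balanced between arms.

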### Sample size calculation

Based on a pilot study [6] we think that radial approach will be associated with a median rate of 5.9% [0.01–12.5;95%CI] of new lesions as detected by cerebral DW-MRI. In patients with aortic stenosis explored by femoral approach we expect a 23% [15–31;95%CI] rate of similar events [3]. With randomization 1:1 an alpha risk of 5% and beta risk of 20% we anticipate a sample size population of 152 patients needed to demonstrate that radial approach could be associated with better outcome concerning the occurrence of silent cerebral infarctions (76 patients in each arm of the study).

### Randomization

After informed consent, eligible patients are randomized 1:1 to a strategy of radial or femoral access. Randomization will be performed at the catheterization laboratory before coronary angiography, by means of randomization list (sealed envelopes) prepared by blocks of 10 patients.

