## Design and methods

### Study design

Prospective multicenter randomized trial (4 centers currently involved: 2 in France, 1 in Italy and 1 in Austria).

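### One published block size of 10, with sealed envelopes used on site by staff who cannot be masked, could make about one allocation in six or seven certain in advance if lists are kept per centre

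*Protocol article*

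**What the plan says.** All of the following is in the protocol article.

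- **Randomization:** "After informed consent, eligible patients are randomized 1:1 to a strategy of radial or femoral access". On place and time: "Randomization will be performed at the catheterization laboratory before coronary angiography". On method: "by means of randomization list (sealed envelopes) prepared by blocks of 10 patients". No other block size is given, and no central step is described.
- **Study design:** four centres in three countries. The article does not say whether they share one list or have one each.
- **Cardiac catheterization:** the operator uses the assigned route, so the operator knows the arm. The article does not use the term open-label; for operators it follows from the procedure.
- **Magnetic resonance imaging:** the two neuroradiologists who read the primary outcome are blinded to the clinical data and unaware of the procedure.
- **Study population:** patients already scheduled for catheterization are invited consecutively, with two exclusion criteria.
- **Sample size calculation:** "we anticipate a sample size population of 152 patients needed", that is "76 patients in each arm of the study".

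**The concern.** In a permuted block with a known size, the last place is always determined, and often so are the places just before it. Someone who has seen the earlier allocations can work them out. Here the people best placed to do so, the catheterization team, see every allocation at their own site. The envelopes are also used where they work, with no described barrier to looking ahead.

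The risk is selection bias: a foreseen arm could influence whether, or in what order, a patient is brought to randomisation. By the article's own Discussion, the traits that might drive such a choice are prognostic. It names procedure length and fluoroscopy time as the factors independently associated with cerebral infarction, and says that aortic atherosclerotic burden raises the risk of catheterization-induced stroke. Masked image reading protects against detection bias but not against this.

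Few events are expected, so the comparison is sensitive to small shifts in who enters which arm.

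**Working it through.** **Inputs from the article.** Block size 10 and ratio 1:1, so m = 5 per arm in each block; 152 patients, 76 per arm; expected rates 5.9% (radial) and 23% (femoral); alpha 5%, power 80%; four centres.

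**Assumptions.** Staff know the block size and every earlier allocation in the current block, which requires one list per centre. Where a centre size is needed, it is 152/4 = 38. The article gives no recruitment by centre.

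**1. The plan's own figure.** The two-sided comparison of 5.9% with 23% at 80% power needs 66 per arm without continuity correction and 77 with it (76.4 before rounding up). The stated 76 per arm is therefore reproduced. The article gives no figure for predictability, so the rest is new calculation.

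**2. Allocations certain in advance, complete blocks.** The last k or more places are determined with probability 2·C(10−k, 5)/C(10, 5):

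| k | Probability |
|---|---|
| 1 | 2·126/252 = 1.000 |
| 2 | 2·56/252 = 0.444 |
| 3 | 2·21/252 = 0.167 |
| 4 | 2·6/252 = 0.048 |
| 5 | 2·1/252 = 0.008 |

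The sum is the expected number of determined places, 2m/(m+1) = 10/6 = 1.67 per block, or 16.7%. Over 152 patients: 152 × 0.1667 = 25.3.

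**3. The same at 38 per centre.** A centre fills three blocks and the first 8 places of a fourth. In the fourth block, only determined places before the last two count: 0.167 + 0.048 + 0.008 = 0.222. Per centre: 3 × 1.667 + 0.222 = 5.22 of 38, or 13.7%. Over four centres: 4 × 5.22 = 20.9.

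**4. Best-guess accuracy.** The strategy is to name the arm with more places left. Expected correct guesses per complete block are m + (2^(2m)/C(2m, m) − 1)/2 = 5 + (1024/252 − 1)/2 = 6.53 of 10, or 65.3%. For the first 8 places of a block, subtract the last place (1) and the ninth (0.444 + 0.556 × 0.5 = 0.722): 6.53 − 1.722 = 4.81. At 38 per centre: (3 × 6.532 + 4.810)/38 = 24.40/38 = 64.2%.

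**5. Alternatives.** The varying-size rows are simulated for 38 per centre, with an observer who knows the set of possible sizes but not the one drawn.

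| Scheme | Certain | Best guess right |
|---|---|---|
| Fixed 10, 38 per centre | 13.7% | 64.2% |
| Random 4/6/8 | 2.4% | 67.6% |
| Random 6/8/10 | 1.7% | 65.8% |
| Random 8/10/12 | 1.6% | 64.5% |
| Fixed 6, complete blocks | 25.0% | 68.3% |
| Fixed 4, complete blocks | 33.3% | 70.8% |

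Varying the size removes nearly all certainty but does not lower the guessing rate. Shorter fixed blocks are worse on both measures.

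**6. Fragility of the result.** Expected events are 76 × 0.059 + 76 × 0.23 = 4.5 + 17.5 = 22. A split of 5 against 17 gives a two-sided Fisher p of 0.010; 7 against 15 gives 0.105. This shows how few events decide the result. It does not estimate bias.

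**The case against.** The strongest reply has four parts.

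- **The figures are conditional.** They need per-centre lists and staff who know the size and keep count. If one list serves all four centres, each site sees only part of a block and predicts less. This stands, and the figures must carry the condition. The block size is public, but the article does not say that sites are told it or use it.
- **The design already narrows the opportunity.** Patients are scheduled beforehand and invited consecutively, they consent before allocation, and the baseline MRI falls within 24 hours before the procedure. This also stands in part: whether and in what order patients reach the laboratory can still vary.
- **Ten is not a bad size as fixed blocks go.** It is less predictable than 4 or 6. True, but it is still one disclosed size.
- **Predictability is not bias.** Correct: nothing in the article allows the size of any bias in the primary endpoint to be estimated, and early opening of envelopes is a possibility, not something the article reports.

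A reader might also infer that the plan wrongly omits stratification by centre, centre in the analysis, and opaque numbered envelopes. The document does not support that. It is a condensed article, and such details are commonly left to the full protocol or analysis plan. Full predictability and centre imbalance from a shared list also cannot both be charged: predictability is greatest when lists are per centre, which is itself stratification by centre.

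**Conclusion.** The point holds in a limited form, and it rests on what the article states: one published block size, sealed envelopes on site, and operators who necessarily know the arm. Given per-centre lists, a known block size and tracked allocations, 21 to 25 of 152 allocations (14% to 17%) are certain in advance and the best guess is right 64% to 65% of the time. With a shared list both figures fall.

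A reader might infer that most allocations are predictable, or that the comparison is already compromised. Neither follows: about one allocation in six or seven is certain at most, and no bias has been shown. What remains is an avoidable weakness in concealment, in a trial with about 22 expected events, that is cheap to remove.

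**What to change.** Allocate centrally by telephone or web, releasing the arm only after the patient has been irrevocably registered. Generate the list with randomly varying block sizes that are not disclosed to sites, for example 6, 8 and 10, and state in the amendment whether lists are kept by centre.

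The central step is the main gain, because it closes the on-site envelope route. Varying the sizes cuts certain allocations from 13.7% to about 2% (about 3 of 152 at 1.7%). It does not reduce best-guess accuracy, which stays at about 66%, so it should not be presented as doing so. Sizes 4, 6 and 8 would do slightly worse on both measures.

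The cost is a new list, a minor set-up for central allocation and a short amendment. The sample size of 152 is unchanged.

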## Discussion

According to previous studies, the rate of stroke after cardiac catheterization ranges from 0.10 % to 0.40 % [22]. However, these studies on the risk of stroke after cardiac catheterization have taken only manifest new neurological deficits as complications. Clinically unapparent damage potentially caused by microscopic air embolism or silent thromboembolism, had not been taken into account. With the advent of DW-MRI, which is very sensitive in detecting acute ischemic lesions within hours after onset [23], it has been shown that asymptomatic embolic events are far more frequent than the apparent neurological complication rate [3-6]. It seems that only the length of the procedure or the procedural fluoroscopy time can be independently associated with the risk of cerebral infarction in these studies. These two parameters are related to the overall influence of the catheter manipulation including additional periods of time while the catheter acts as a embolic source because it may lead to thrombus formation or affect the vessel wall during manipulation or placement in the patient's vascular system. It has also been suggested that silent acute brain injury can be increased using trans-radial access [5] but this has not been demonstrated.

Because all cardiac catheterizations are associated with microembolism as detected by TCD it has been suggested that most of these microembolism might be microbubbles and are therefore likely to be benign. However some recent publications, mentioned above, raise the possibility that some microparticles embolized during heart catheterization could be responsible for acute brain injuries. In fact, the most likely sources of embolic material are catheters and guidewires that dislodge atheromatous material from the aorta [24]. Visible aortic debris may be seen upon withdrawal of catheters during PCI cases [25]. Patients with a large atherosclerotic burden in the aorta as documented by transesophageal echocardiography, such as those with advanced coronary artery disease, have an increased risk of cardiac catheterization-induced stroke [12]. It has been shown that patients with cardiac catheterization-induced stroke often have multiple acute lesions on DW-MRI (often tiny, cortical, and in different vascular territories), distinct from the occasionally symptomatic lesion, and consistent with a shower of embolic material.

Silent cerebral infarction might be a major concern during cardiac catheterization and its potential relationship with cognitive decline needs to be assessed prospectively in a multicenter study. In the SCIPION trial we will use serial DW-MRI to assess the rate of silent cerebral infarction after cardiac catheterization and we will compare the impact of the arterial access site (radial or femoral) on this emerging phenomenon.
